## Abstract

**Background:**

There is an emerging body of evidence that links exposure to shift work to cardiovascular disease (CVD). The risk of coronary events, such as myocardial infarction, is greater among night shift workers compared to day workers. There is reason to believe that repeated exposure to shift work, especially night shift work, creates alterations in normal circadian patterns of blood pressure (BP) and heart rate variability (HRV) and that these alterations contribute to increased risk of CVD. Recent data suggest that allowing shift workers to nap during night shifts may help to normalize BP and HRV patterns and, over time, reduce the risk of CVD. The risk of CVD related to shift work is elevated for emergency medical services (EMS) shift workers due in part to long-duration shifts, frequent use of night shifts, and a high prevalence of multiple jobs.

**Methods:**

We will use a randomized crossover trial study design with three study conditions. The targeted population is comprised of EMS clinician shift workers, and our goal enrollment is 35 total participants with an estimated 10 of the 35 enrolled not completing the study protocol or classified as lost to attrition. All three conditions will involve continuous monitoring over 72 h and will begin with a 36-h at-home period, followed by 24 total hours in the lab (including a 12-h simulated night shift), ending with 12 h at home. The key difference between the three conditions is the intra-shift nap. Condition 1 will involve a simulated 12-h night shift with total sleep deprivation. Condition 2 will involve a simulated 12-h night shift and a 30-min nap opportunity. Condition 3 will involve a simulated 12-h night shift with a 2-h nap opportunity. Our primary outcomes of interest include blunted BP dipping and reduced HRV as measured by the standard deviation of the inter-beat intervals of normal sinus beats. Non-dipping status will be defined as sleep hours BP dip of less than 10%.

**Discussion:**

Our study will address two indicators of cardiovascular health and determine if shorter or longer duration naps during night shifts have a clinically meaningful impact.

**Trial registration:**

ClinicalTrials.gov NCT04469803. Registered on 9 July 2020

**Supplementary Information:**

The online version contains supplementary material available at 10.1186/s13063-021-05161-4.

## Introduction

### Background and rationale {6a} {6b}

There is an emerging body of evidence that links exposure to shift work to cardiovascular disease (CVD) [1]. The incidence of hypertension (HTN) is higher among shift workers compared to persons who work traditional daylight schedules [2, 3]. Shift workers have a 23% higher risk of myocardial infarction and a 5% higher risk of stroke relative to day workers [4, 5]. In addition, the risk of coronary events (e.g., myocardial infarction, coronary mortality, hospital admission due to coronary artery disease) is greater among night shift workers compared to day workers (risk ratio 1.41, 95%CI 1.13, 1.76) [5]. There is reason to believe that repeated exposure to shift work creates alterations in the normal circadian patterns of blood pressure (BP) and heart rate variability (HRV) and that these alterations contribute to increased risk of CVD over time [6, 7]. There is also reason to believe that allowing shift workers to nap on duty (especially during night shift work) may help to normalize BP and HRV patterns and over time reduce the risk of CVD due in this population [8, 9].

Shift work refers to work schedules outside the traditional daylight schedule (e.g., 9 am to 5 pm) [10]. Paramedics and emergency medical technicians (EMTs) are shift workers within the United States Emergency Medical Services (EMS) system, which comprised more than one million certified/licensed personnel and approximately 20,000 EMS agencies nationwide [11]. The clinician shift workers who work in EMS are often deployed in crews of two and frequently work night shifts, evening shifts, long-duration shifts (e.g., 24 h and 48 h), and rotating or irregular shift schedules [12]. Shift work contributes to fatigue, excessive daytime sleepiness, and problems with obtaining adequate sleep [13, 14]. Previous research shows that three quarters of EMS shift workers report occupational fatigue, greater than half report poor sleep quality, half report inadequate recovery between scheduled shifts, and half report sleeping less than 6 h per night [15–19].

Shift work forces prolonged wakefulness and disrupts a number of biological, chemical/hormonal, and physiologic mechanisms that are closely tied to the night/day, sleep/wake cycle (circadian rhythms) [20, 21]. The normal circadian pattern of BP is characterized by elevations during daylight hours and wakefulness, followed by a decrease of 10–20% during nighttime hours and sleep [9, 22]. This decrease in BP during sleep and nighttime hours is referred to as the “dip” [9, 22]. Blunting of the BP dip occurs when BP fails to drop by 10% during nighttime hours or during sleep [9, 22]. In select populations, blunted BP dipping during sleep and nighttime hours has been linked to select demographic and physiologic factors, elevated levels of stress, stroke, target organ damage, left ventricular hypertrophy, progressive renal damage, and cardiovascular mortality [23–31]. Previous research of night shift workers (e.g., physicians and nurses) shows that nighttime BP is often elevated compared to daytime values [32, 33], and in some cases, the BP dip is blunted during shift work and during recovery immediately after shift work [34]. Our recent study of 56 EMS clinicians shows that a large proportion of those who work night shifts experience blunted BP dipping during shift work [35].

Previous research also shows an association between shift work and unhealthy HRV patterns [36–39]. Healthy HRV may be characterized by oscillations in the heart rate and beat-to-beat fluctuations that are more variable over a 24-h period [40–42]. Greater variability in patterns of HRV signifies balance between sympathetic and parasympathetic activity and is often associated with better health, better performance, and increased ability to respond to, and cope with stress [41]. Decreased variability, or reduced HRV, may be a marker of increased sympathetic activity and reduced parasympathetic activity. Prolonged periods of reduced HRV have been linked to acute cardiac events and all-cause mortality [43, 44]. One study of 14 EMTs revealed reduced levels of HRV during periods of sleep that occurred during shift work versus during sleep on non-workdays [39]. A study of nine paramedics in Japan showed an abnormal HRV pattern during the workday compared to the non-workday [45]. A separate study of 14 male firefighter-paramedics in Finland reported decreased variability in heart rate during a 24-h shift followed by normalization to healthier levels after 3 days of rest [36]. Together, these studies suggest that shift work may have a negative impact on the normal circadian pattern of HRV among EMS shift workers.

Shift work is essential for many occupations, including public safety workers such as police, fire, and EMS, which provide critical services that must be available all hours, day and night [46]. Many EMS employers would likely object to policies that restrict shift duration or timing as a means to guard against the impact of shift work on cardiovascular health [47]. Employers are more likely amenable to strategies that allow for shift work to continue and simultaneously reduce its impact on select outcomes. One such strategy is napping during shift work. Napping has been described as “sleep periods at least 50% shorter than an individual’s average nocturnal sleep length” [48, 49]. A recent systematic review and meta-analysis shows that napping during night shifts has a positive impact on shift worker’s subjective ratings of sleepiness and fatigue [50]. Evidence-based guidelines for fatigue risk management in EMS promote napping during shift work, especially during night shifts [51]. These data and guidance support intra-shift napping as it pertains to worker safety [51]. However, previous research devoted to the health benefits of intra-shift napping is limited. Employers face a great deal of uncertainty when weighing the risks versus benefits of intra-shift napping, and uncertainty regarding implementation.

### Objectives {7}

In this paper, we present the study protocol for an experimental study of EMS shift workers using intra-shift napping during simulated night shifts. We will use a randomized crossover study design comprised of two intra-shift napping conditions and one no-nap comparison condition. With this design, we first aim to determine the impact of different durations of napping during night shifts on BP dipping and HRV during sleep and during nighttime hours. Second, we aim to determine if longer duration naps are associated with improved recovery or a more rapid normalization of BP and HRV patterns post-shift work. We hypothesize higher odds of blunted BP dipping during the no-nap condition versus the napping conditions. We hypothesize that when compared to the napping conditions, select HRV measures taken during the no-nap condition (i.e., the standard deviation of the inter-beat intervals of normal sinus beats, SDNN) will be reduced. We hypothesize that BP and HRV patterns observed immediately following the simulated night shift for both napping conditions will normalize sooner than observed for the no-nap condition. Finally, we hypothesize that for both BP and HRV, the greatest benefit will be observed in the longer duration nap of 2 h versus the shorter 30-min nap condition.

### Trial design {8}

We will use a randomized crossover trial study design with three study arms/conditions. All three conditions will involve continuous monitoring over 72 h and will begin with a 36-h at-home period, followed by 24 total hours in the lab (including a 12-h simulated night shift), and ending with 12 h at home. The key difference between the three conditions is the presence or absence of an intra-shift nap and the duration of that nap. Condition 1 will involve a simulated 12-h night shift with no nap: total sleep deprivation. Condition 2 will comprise another simulated 12-h night shift and a 30-min nap opportunity. Condition 3 will involve a simulated 12-h night shift and a 2-h nap opportunity. There will be a mandatory 1–3 week washout period between conditions. The order in which participants complete the study conditions will be balanced by a William’s square design. In the paragraphs below, we outline the details of our experimental study in accordance with the CONSORT/SPIRIT statement. Figure 1 illustrates the flow chart of our trial, and Fig. 2 illustrates the SPIRIT template for enrolment, intervention, and assessment. The University of Pittsburgh Institutional Review Board (IRB) approved this study {24}, and our protocol has been registered with ClinicalTrials.gov ({2a} registration number: NCT04469803; public release date: 9 July 2020). All subjects are required to provide written informed consent (see Additional file 1, which reports on all elements of the SPIRIT checklist). All elements of the World Health Organization Trial Registration Data Set can be found in this article, supplemental file, and the ClinicalTrials.gov registration.

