### Eligibility criteria {10}

Inclusion criteria include the following: (A) a commitment to 72 h of continuous monitoring on three separate occasions; (B) a commitment to complete a laboratory-based simulated 12-h night shift during each 72-h period; (C) a commitment to going without sleep for at least one of the simulated night shifts; (D) a commitment to wearing multiple monitoring devices (i.e., Holter monitors, blood pressure monitors) during each of the 72 h of monitoring; (E) a commitment to abstain from exercise, caffeine, alcohol, and nicotine during the 72-h study interval and to follow a structured sleep and food consumption protocol for 72 consecutive hours during each visit; (F) confirmation of current licensure/certification as an EMS clinician (i.e., EMT, paramedic, flight nurse, or other first responder); (G) confirmation of current work as a front-line clinician (with full-time administrators excluded); (H) lack of known medical conditions that may impact findings (i.e., a sleep disorder, hypertension, CVD, history of myocardial infarction or stroke, kidney disease, liver disease, adrenal disease, thyroid disease, rheumatologic disease, hematologic disease, cancer, or organ transplantation); (I) not known to be pregnant; (J) confirmation of no physical conditions that may prevent wearing of multiple monitoring devices; and (K) age 18 years or older.

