### Relevant concomitant care permitted or prohibited during the trial {11d}

During the study protocol, participants will be asked to not engage in scheduled or unscheduled shift work and avoid consumption of caffeine or alcohol and avoid nicotine. Two out of seven similar studies testing the impact of two different nap durations have allowed participants to consume one caffeinated beverage or smoke a cigarette at select points during the study protocol [56–66]. Caffeine is a stimulant that has a profound impact on subjective sleepiness and alertness [67] and therefore may impact the differences between study conditions. While previous research has assessed the interaction between caffeine and napping [68], that is not the focus of this protocol.

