### Statistical methods

#### Statistical methods for primary and secondary outcomes {20a}

We will report the demographic characteristics of the study sample using descriptive statistics and stratify the final dataset into two categories for the main analysis. These categories will be labeled as “complete” and “incomplete data.” We will further describe the average systolic and diastolic BP, the incidence of blunted BP dipping, and the proportion of participants with blunted BP dipping. Blunted nocturnal BP dipping will be defined as previously described. Our second outcome of interest is HRV. As prescribed [72], we will examine HRV based on five time-based measures summarized over each 24-h period of observation.

To address the impact of napping on BP dipping, we will conduct paired *t* tests to determine if the mean amount of BP dipping differs across conditions. Generalized linear mixed models (GLMM) with participant-specific random effects will be utilized to compare the odds of blunted BP dipping across conditions. We will evaluate the distribution of residuals at each level of the models for linearity and heterogeneity. We will check for outliers and influential observations and sets of observations. The distribution of the data will be examined, and transformations will be performed as necessary for valid comparisons. We will use GLMM to estimate and compare the proportion of EMS workers with blunted BP dipping and control for the dependence between repeated measures within each participant with a random subject effect.

To address the impact of napping on select measures of HRV, we will use GLMM with appropriate distribution and link function to estimate and compare HRV measures between EMS workers across the three conditions. We will again account for the within-participant correlation of repeated measurements and any participant-dependent covariates that vary in the study sample. The least square means and corresponding 95% confidence intervals will be calculated from the models for each group and the difference between groups.

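### No stated nap comparison names a session-specific baseline, although every session records one before the nap; adjusting for it could recover precision at little cost

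*Protocol article*

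**What the plan says.** - **Session structure.** Each condition "will begin with a 36-h at-home period, followed by 24 total hours in the lab (including a 12-h simulated night shift"), then 12 h at home (Trial design {8}). Outcomes {12} assesses dipping in all periods of observation and summarises HRV over each 24-h period, so the at-home run-in is measured every time.
- **Who takes part.** Eligibility criteria {10} requires "confirmation of current work as a front-line clinician (with full-time administrators excluded"). The Background says such clinicians frequently work nights and shifts of 24 to 48 h.
- **Limits on real work.** During the study protocol, "participants will be asked to not engage in scheduled or unscheduled shift work" (section {11d}). No shift-free interval before hour 0 is stated. Trial design adds: "There will be a mandatory 1–3 week washout period between conditions". It does not say that real shifts stop in that time.
- **Residual effects.** The Background cites a study of 14 male firefighter-paramedics that found "decreased variability in heart rate during a 24-h shift followed by normalization to healthier levels after 3 days of rest".
- **Analysis {20a}.** Mean BP dip is compared by paired t tests. The mixed model for blunted dipping will "control for the dependence between repeated measures within each participant with a random subject effect". The HRV models add unspecified participant-dependent covariates, and the recovery-slope models add time-dependent ones. None names a session baseline.

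**The concern.** A crossover removes stable differences between people. It does not remove a state that changes between one person's sessions. A clinician who finishes a real night shift just before one session and comes from days off before another brings such a difference into the nap contrast. A random subject effect is constant over the three sessions and cannot absorb it; nor can a paired t test.

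The trial records BP dip and HRV in each session before the nap conditions diverge. Leaving that information out of the between-condition tests gives up precision in a study planned around 25 completers with almost no power in reserve. It also leaves the return to normal in the second objective without a stated pre-shift reference.

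**Working it through.** **Inputs from the power statement in {20a}:** 25 participants, difference 5 mmHg, within-participant SD 6 mmHg, two-sided alpha 0.05, power 80%. **Assumed:** ρ, the within-participant correlation between a session's baseline and its outcome, and τ, any extra session-to-session SD from recent shifts. The documents give neither.

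**1. The planned figure.** SD of a paired difference = 6 × √2 = 8.49 mmHg. An exact paired t test (noncentral t) needs n = 25 and has 80.7% power at 25, so the stated number reproduces. (The text names a z test in Poisson regression, which cannot be run from the stated inputs because no rate is given.)

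**2. Bias or noise?** In a simulation of 24 participants (40,000 runs, no nap effect), a random half of sessions carried a shift residue of R units.

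| R | Bias | Type I error | SD of estimated difference |
|---|---|---|---|
| 0 | −0.001 | 5.0% | 1.73 |
| 5 | −0.019 | 4.9% | 1.87 |
| 10 | 0.011 | 5.0% | 2.25 |

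The algebra agrees. The residue adds variance R² × 0.5 × 0.5, so for R = 5 the SD is √(36 + 6.25) = 6.50 and the SD of the estimate is 6.50 × √2 / √24 = 1.88. For R = 10 it is √(36 + 25) × √2 / √24 = 2.25. Residue unrelated to condition costs precision and leaves the contrast centred.

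**3. Size, if the residue is not already in the 6 mmHg.** Total SD = √(36 + τ²).

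| τ (mmHg, assumed) | Total SD | n for 80% | Power at 25 |
|---|---|---|---|
| 2 | 6.32 | 28 | 76.5% |
| 3 | 6.71 | 31 | 71.5% |
| 4 | 7.21 | 35 | 65.3% |

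**4. What adjustment could recover.** As a covariate, the residual SD is 6√(1 − ρ²). As a change score, with equal baseline and outcome variances, it is 6√(2(1 − ρ)). Both are multiplied by √2 for the paired difference.

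| ρ (assumed) | Covariate: SD, n, power at 25 | Change score: SD, n, power at 25 |
|---|---|---|
| 0.1 | 5.97, 25, 81.1% | 8.05, 43, 55.9% |
| 0.3 | 5.72, 23, 84.2% | 7.10, 34, 66.6% |
| 0.5 | 5.20, 19, 90.4% | 6.00, 25, 80.7% |
| 0.7 | 4.28, 14, 97.7% | 4.65, 16, 95.4% |

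Subtraction breaks even with no adjustment where 2(1 − ρ) = 1, that is at ρ = 0.5, and loses power below it. These figures ignore the degrees of freedom spent on the covariate terms. They apply to continuous outcomes only, not to the odds of blunted dipping.

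**5. Is there a usable baseline block?** Taking the lab phase as 1900 to 1900, hour 0 is about 0700. The fixed night window, 2300 to 0659, then falls in hours 16 to 24. The first 24 h therefore hold one complete night and one 24-h HRV summary, ahead of the simulated shift at about hour 36.

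**The case against.** Three stronger readings are tempting, and the documents support none of them.

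- **That the 36-h run-in is too short.** It is half of the cited 3 days (36/72). But that figure comes from one study of 14 men after a 24-h shift, concerns HRV only, and reports when normalisation was seen, not the least time needed. The outcomes also come later: the nap window falls at about hours 43 to 45 and post-shift recovery at hours 48 to 72. The citation makes residue at 36 h plausible and no more.
- **That recent shifts bias the nap contrasts.** Order follows a randomised Williams design, so earlier work should be unrelated to condition. Chance imbalance is what alpha already covers.
- **That the baseline is ignored altogether.** The at-home data are measured and summarised, and the HRV and recovery models leave their covariates open. A covariate list is commonly left to an analysis plan, which is not shown here.

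Other points count in the plan's favour. The bar on shift work could be read more widely than the 72 h. Participants follow a structured sleep and food schedule and abstain from exercise, caffeine, alcohol and nicotine. Circadian alignment is estimated for each sleep episode. The 6 mmHg SD is described as similar to earlier work, so it may already contain some residue. Hours 0 to 24 are also an imperfect proxy for the state at hours 43 to 72.

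All of this stands and limits the point to precision. It does not answer the paired t test: that is a stated method with no place for a covariate, applied to the quantity on which the trial is powered. An analysis plan could bring in the baseline only by replacing it.

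**Conclusion.** The point holds as one of efficiency. The protocol collects a session-specific baseline three times per participant, fixes a test for mean BP dip that cannot use it, and names it in no other cross-condition model. Validity is not threatened.

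The gain rests on an undocumented correlation. Against 80.7% as planned, power at 25 is about 81% at ρ = 0.1 (practically nothing), 84% at 0.3 and 90% at 0.5. The possible loss from shift residue (power of 76.5% to 65.3% for an added SD of 2 to 4 mmHg) is likewise an assumed range, and applies only so far as the 6 mmHg excludes it. How often participants come to a session straight from a real shift is unknown; the documents only leave it open.

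**What to change.** 1. **Continuous outcomes (BP dip, SDNN and the other HRV measures).** Replace the paired t test with a linear mixed model. In it and in the HRV models, include the value of the same measure from the first at-home 24 h, as two terms: the participant's mean baseline over sessions, and the session's deviation from that mean. The deviation carries the session-specific adjustment. Do not use a change score.
2. **Role of that block.** Treat hours 0 to 24 as baseline in these comparisons. They can still be described with the other periods.
3. **Blunted dipping (binary).** Use the baseline terms only in a sensitivity analysis, given about 25 completers.
4. **Recent work.** On the existing device-application form, record the end time and length of the last real shift, and add a sensitivity analysis adjusting for time since that shift.
5. **Timing of allocation.** The legend of Fig. 2 counts hours from allocation with 0 at the start of the at-home phase, and section {16b} opens the envelope when each session begins. Confirm that it is opened after the baseline block, or state that the baseline may be measured with allocation known.

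The cost is about two degrees of freedom per model, revised model wording and one line on a form. No visit or measurement is added and the 36-h schedule is unchanged.
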